## Abstract

**Background:**

Staffing ratios in nursing homes vary among the federal states of Germany, but there are no rational grounds for these variations. In a previous study, a new instrument for the standardized calculation of staffing requirements in nursing homes was developed (*Algorithm*
1.0). The development was based on a new empirical data collection method that derives actual and target values for the time and number of care interventions provided. *Algorithm*
1.0 found an increased requirement of 36% of staff in German nursing homes. Based on these results, the German legislature has commissioned a model program to trial and evaluate a complex intervention comprising increased staffing combined with strategies for organizational development.

**Methods:**

The mixed-methods study consists of (i) developing a concept for restructuring the work organization, (ii) the application of this concept combined with increased staffing in 10 nursing homes (complex intervention), and the further development of the concept using a participatory and iterative formal evaluation process. The intervention consists of (a) quantitative measures of increased staffing based on a calculation using *Algorithm*
1.0 and (b) qualitative measures regarding organizational development. The intervention will be conducted over one year. The effects of the intervention on job satisfaction and quality of care will be evaluated in (iii) a comprehensive prospective, controlled summative evaluation. The results will be compared with ten matched nursing homes as a control group. Finally, (iv) prototypical concepts for qualification-oriented work organization, a strategy for the national rollout, and the further development of *Algorithm*
1.0 into *Algorithm 2.0* will be derived.

**Discussion:**

In Germany, there is an ongoing dynamic legislation process regarding further developing the long-term care sector. The study, which is the subject of the study protocol presented here, generates an evidence-based strategy for the staffing requirements for nursing homes.

Ethics and dissemination.

This study was approved by the Ethics Committee of the German Association of Nursing Science (Deutsche Gesellschaft für Pflegewissenschaft) on 02.08.2023 (amended on 20.09.2023). Research findings are disseminated through presentations at national and international conferences and publications in peer-reviewed scientific journals.

**Trial registration number**: German Clinical Trails Register DRKS00031773 (Date of registration 09.11.2023).

## Introduction

In most of Europe, the policy affecting the organization and provision of long-term care (LTC) has to face several socio-cultural and economic challenges [1]. Ageing societies, a shortage of skilled workers, and the aim to maintain a high quality of care are just some of them [2, 3]. There is a demand for the evidence-based development of new approaches for the organization of LTC. However, there is not only a wide range of political prerequisites but also a variety of methodological approaches measuring staffing ratios, quality of care, and, for example, job satisfaction in LTC facilities, making it difficult to evaluate the direct correlation between these parameters [4, 5].

An established way to assess the quality of care in LTC facilities is to apply quality indicators, and a growing number of countries report quality indicators publicly [6, 7]. Frequently reported indicators are related to resident safety outcomes like pressure ulcers, falls, physical restraints, and weight loss [7, 8]. In Germany, the public reporting system was revised in 2019 and now comprises the results of i) scientifically developed quality indicators [9] (Table 2), ii) external quality audits (Table 2), and iii) additional information about the nursing home (e.g., the accessibility of the care facility, the possibility of a trial stay or the staffing levels). Job satisfaction is essential to nursing home staff retention, and evidence indicates a correlation between job fluctuation and quality of care [10, 11]. Stress and low staffing levels are the most prominent reasons for job dissatisfaction among LTC staff and are still growing [12, 13].

### Objectives

This pilot program has three central aims. The first is the participatory development of a qualification-oriented work organization, trialing them combined with increased staffing (according to *Algorithm*
1.0) and evaluating the effects of this combination. The new work organization strategy is characterized by assigning work tasks individually according to the qualification of the nursing home staff (qualification orientation). The second aim is to derive a strategy for the national rollout of the implementation of qualification-oriented work organization from the evaluation findings. The third objective of the study is to refine *Algorithm*
1.0 under the condition of new work organization based on the data from the evaluation and parameterize it to yield *Algorithm 2.0*.

Our working hypothesis is that increased staffing, combined with a new work organization that matches the staff's qualifications with the resident’s care needs, can improve job satisfaction and quality of care as defined in the methods section.

## Background

This study protocol describes a study conducted by legal mandate after a Europe-wide call for tenders. The study aims to derive a strategy affecting the work organization in German nursing homes. The legal background in Germany and the underlying data collection method are crucial to understanding the study subject to this study protocol.

## Legal background in Germany

According to Paragraph 69, Sentence 1 of the German Social Code, Part 11, LTC insurance must provide needs-oriented care in Germany. That means that the provision of care must center the person’s care needs instead of, for example, centering the health care system’s resources. Determining care needs again is defined in Paragraph 14 of the German Social Code, Part 11. According to this Paragraph, the detection of care needs is based on the extent of (physical, cognitive, or psychical) independence impairments. A standardized instrument for assessing the need for LTC (‘*Pflegegutachten*’) was developed, described in Paragraph 15 of the German Social Code, Part 11. Applying this instrument, the assessors and evaluators on behalf of the LTC insurance funds (‘*Medizinischer Dienst’*) classify every person needing long-term care into one of five different care grades (with care grade one indicating the lowest and care grade 5 indicating the highest level of care dependence). Paragraph 113c of the German Social Code, Part 11 again describes the financing of staffing ratios in nursing homes. These upper limits are calculated based on the care grades so that more staff can be financed when higher care grades are present in the respecting nursing home (note that the term ‘nursing home’ in Germany refers to inpatient long-term care). In Sects. 1–3, the Paragraph distinguishes between three qualification groups for the financing of nursing home staff: i) unqualified nurses (‘*Hilfskräfte’*), ii) semi-qualified nurses (‘*Assistenzkräfte’*), and iii) qualified nurses (‘*Fachkräfte’*).

The legally defined and highly standardized procedure described in the Paragraphs mentioned above is valid in all the states (‘*Länder*’) of Germany. However, Paragraph 75 Sect. 3 of the German Social Code, Part 11 specifies that lower staffing limits must be negotiated on a state level. Due to the different financial resources of the countries, de facto staffing ratios in nursing homes vary among the federal states of Germany. However, there is no significant difference in the distribution of care grades between the states [14]. Considering that the mean time required to provide needs-oriented care derives from the care grade, staffing ratios should not vary, and there are no rational grounds for existing disparities [15].

## Qualification Levels (QL) in LTC

As seen above, German legislation applies three qualification groups to finance nursing home staff. This is based on the previous study, ‘PeBeM1’ (see below), in which a system was developed that applies the broad definitions of the National Qualification Framework (DQR) derived from the European Qualification Framework (EQF) to nursing homes [16, 17]. It creates specific definitions of Qualification Levels on a national level in the given setting (Qualification-Mix-Model; QMM). Furthermore, the QMM determines the minimum QL for the appropriate care provision for every distinct intervention included in an Intervention Catalogue [18]. The normative assignment of a targeted QL to the interventions was approved by the Quality Assurance Committee (‘*Qualitätsausschuss’*) according to Paragraph 113b of the German Social Code, Part 11.

Table 1 shows the relationship between the internationally recognized European Qualification Frame (EQF), the QL applied in the PeBeM studies, and the qualification groups of Paragraph 113c of the German Social Code, Part 11.

**Table 1 Tab1:** Comparison between the European Qualification Frame, QL based on Darmann-Finck. (2021), and qualification groups of the German Social Code

European Qualification Frame (EQF)^a^	QL, according to the PeBeM study (see Darmann-Finck 2021)	Paragraph 113c of the German Social Code, Part 11
Level 1: ▪ Basic general knowledge, ▪ Basic skills required to carry out simple tasks, ▪ Work or study under direct supervision in a structured context	QL 1: Employees without training, after four months of supervised work	unqualified nurses
Level 2: ▪ Basic factual knowledge of a field of work or study, ▪ Basic cognitive and practical skills required to use relevant information in order to carry out tasks and to solve routine problems using simple rules and tools, ▪ Work or study under supervision with some autonomy	▪ QL 2 (care): 2–6-month introductory nursing course (at least 150 h)^b^ and a total of at least one year of supervised work ▪ QL 2 (supervision and support): Caregivers with 160 h lessons and three weeks internship	
Level3: ▪ Knowledge of facts, principles, processes, and general concepts in a field of work or study, ▪ A range of cognitive and practical skills required to accomplish tasks and solve problems by selecting and applying basic methods, tools, materials, and information, Take responsibility for the completion of tasks in work or study; adapt own behavior to circumstances in solving problems	QL 3: Nursing assistants with one or two years of training (according to state-specific training regulations)	semi-qualified nurses
Level 4: ▪ Factual and theoretical knowledge in broad contexts within a field of work or study, ▪ A range of cognitive and practical skills required to generate solutions to specific problems in a field of work or study, ▪ Exercise self-management within the guidelines of work or study contexts that are usually predictable but are subject to change; supervise the routine work of others, taking some responsibility for the evaluation and improvement of work or study activities	QL 4: Nursing staff with at least three years of full-time vocational training	qualified nurses
Level 5: ▪ Comprehensive, specialized, factual, and theoretical knowledge within a field of work or study and an awareness of the boundaries of that knowledge ▪ A comprehensive range of cognitive and practical skills required to develop creative solutions to abstract problems ▪ Exercise management and supervision in contexts of work or study activities where there is unpredictable change; review and develop the performance of self and others	▪ QL 5 (specialist): Nursing staff with at least 160 hours^b^ of theoretical training (e.g., palliative care, geriatric psychiatry, wound management) following the state-specific training regulations and two years of work experience ▪ QL 5 (management): Nursing specialist with further training for management tasks (at least 460 h of theoretical instruction)	
Level 6: ▪ Advanced knowledge of a field of work or study involving a critical understanding of theories and principles ▪ Advanced skills, demonstrating mastery and innovation, required to solve complex and unpredictable problems in a specialized field of work or study ▪ Manage complex technical or professional activities or projects, taking responsibility for decision-making in unpredictable work or study contexts; take responsibility for managing the professional development of individuals and groups	QL 6: Nursing specialist with a Bachelor's degree (primary qualifying degree, management studies, or similar)	

^a^Further levels 7 and 8 are part of the systems but are omitted in the comparison

^b^Note that the definition is based on Darmann-Finck 2020 but further developed

## PeBeM data collection method and *Algorithm*1.0

In 2020, a new standardized data collection method was developed and applied within the study ‘Development of a scientifically based procedure for the standardized calculation of staffing requirements in long-term care (PeBeM 1)’. The aim of the study was the development of an instrument that was able to calculate the quantity (in terms of the number) and quality (in terms of the qualification) of required nursing home staff (PeBeM is an acronym for the German word *Personalbemessung* – calculation of staffing ratios). That instrument is called *Algorithm* 1.0 [15].

The PeBeM data collection method consists of three core elements:Compiling a new assessment of the need for LTC (‘Pflegegutachten’). Within the PeBeM data collection method, experts from the respective assessors and evaluators, on behalf of the LTC insurance funds (i.e., Medizinische Dienste/medicproof GmbH), apply this assessment to gain actual information about the care and health conditions of nursing home residents.Preparing a care intervention plan that follows the day's structure (‘daily intervention planning’, DIP). Scientists from the study team (who also have an exam in nursing) and nurses from the respective nursing homes tailor an individual DIP for every resident. All available and relevant information about the care-dependent person is brought together. The aim of this step is the detailed depiction of the dependents' individual care needs and the planning of all necessary care interventions for the data collection period.The shadowing of the nursing staff. The care provision is observed in the nursing home for about one week. While working, the facility's nursing staff is accompanied by a data-collecting shadower (also qualified nursing staff) on a one-to-one basis. The shadowers document the interventions in real-time and the time needed on an electronic device (tablet computer). The QL of the nursing staff is documented automatically by the software. All interventions planned in the DIP appear on the tablet computer screen and must be documented regarding the actual. The system gives time stamps for the duration of documentation when the shadowers start and stop the observed intervention. If an intervention is not provided, the shadowers document a reason. Additionally, they rate the time spent (in terms of surcharges or deductions) and the number of interventions (that is, they state whether a provided intervention was unnecessary or a necessary intervention was not provided).

The PeBeM data collection method is the first standardized, evidence-based data collection method that combines empirical and normative elements and provides data with information about i) number, ii) duration, and iii) qualification on both the actual and the target level. The comparison of the targeted QL (required by the complexity of the residents’ care and health status) and the actual QL from the nursing home staff that provided the care intervention derives the level of QL fitting. These levels are i) fitting (i.e., the QL is as high as required), ii) overqualified (i.e., the QL is higher than required), or iii) underqualified (i.e., the QL is lower than required). Reducing the difference between IS and OUGHT values of number, duration, and qualification can be interpreted as improving the quality of care.

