## Summative evaluation

The customized concepts will be practiced, refined, and evaluated in the third study phase. The evaluation is planned as a prospective interventional study. In the intervention group, all elements of the data acquisition for the summative evaluation will take place as pre-post-comparison at two points in time (t_0_ before the intervention and t_1_ after the implementation of the changes in organization and staffing) at an interval of one year (note that the shadowing only takes place in one living area per care home). To control for general trends in the dynamic LTC setting and the effects of the revision of Paragraph 113 Section C of the German Social Code, Part 11 (that enacted a new finance of staffing ratios based on *Algorithm*
1.0) 10 nursing homes from the intervention group are matched with ten nursing homes in the control group by state, number of beds, and ownership. The control group undergoes the surveys of the summative evaluation but not the shadowing nor the two intervention measures. A (cluster) randomization was not possible due to the stipulations of the statutory order.

The summative evaluation assesses the effects of the intervention on (i) quality of care, (ii) job satisfaction, and (iii) changes in the difference between (a) the number of provided interventions, (b) the duration of the provided interventions, and (c) the extent of qualification-fitting. Table 2 provides an overview of the data collection methods for the endpoints of the summative evaluation.

**Table 2 Tab2:** Data collection methods for the endpoints of the summative evaluation

Methods and instruments	Operationalization of the endpoints

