Thirdly, empirical data will be collected in one living area of each nursing home of the intervention group in an observational study (‘shadowing’). The methodology was developed in the first PeBeM study and described in the final report [15]. The three elements of the data collection method are described in the background section. To assess actual-target differences (and their changes from t_0_ to t_1_), the shadowing data will be analyzed about (i) the number of interventions provided, (ii) the duration of the interventions provided, and (iii) the extent of qualification fitting. The determination of the respecting values is shown in Table 3.

**Table 3 Tab3:** Determination of actual and target data of care provision in the shadowing

Information provided in the data	Determination of the actual value	Determination of the target value	Involved Determiner
**Number** of provided interventions	Electronic time stamp while shadowing	1. DIP	1. Members of the study team qualified as a nurse
		2. Shadowers assessment	2. Shadowers
**Duration** of the provided interventions	Electronic time stamps while shadowing	Shadowers assessment	Shadowers
Extent of **qualification fitting**	Automatic electronic documentation while shadowing (data link in software between nursing staff and QL)	1. Software derives automatically from BI	1. Assessors and evaluators on behalf of the LTC insurance funds
		2. Software derives automatically from DIP (if additional information was registered)	2. As nurse-qualified members of the study team determine QL requirements individually

Fourthly, a partly standardized online questionnaire will be developed to assess the shadower's perception of the cooperation and communication structures within the nursing homes. The survey will be created based on experience from the PeBeM1 project.

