## Prototypical concepts, strategy for a national rollout, and Algorithm 2.0

The study has three superordinated aims. The first is the participatory development of prototypical concepts for qualification-oriented work organization. According to individual nursing home characteristics like the care organization model, competency profiles of the staff, or the extent of digitalization, typed concept variants will be derived. The prototypical concepts thus consider different starting points of nursing homes and offer different development paths for various nursing homes. The definitive attributes that distinguish nursing homes with comparable preconditions will be analyzed using the iterative formal evaluation. These concepts, after rollout, can serve as templates for any nursing home from those to choose the most appropriate. Once one of the typed concepts is selected, any nursing home is free for individual adaptation. Due to the small sample size, the methodology for the analysis must be qualitative. However, the structure of the formative evaluation will take shape during the project. The final nursing home-typed concepts include procedures for a standardized census of the actual status as well as instruments and materials that depend on the prototype of the nursing home. The second final objective of the study aims to incorporate all the results and findings from project steps 1–4 and the contemporaneous participatory co-creative processes to parameterize *Algorithm 2.0*. Data from the shadowing (particularly the number of staff and data on the targeted duration of specific tasks and procedures) are analyzed to refine the algorithm. New aspects compared to *Algorithm* 1.0 will be (i) the incorporation of QLs 5 + and other professions in the calculation and (ii) target time values for indirect care and occasional care interventions. The third final objective is to develop a strategy for the national rollout. Methodological and substantive aspects for developing the nationwide rollout must be created during the project. The method under consideration is focus groups.

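### The plan reads any narrowing of the actual-target gap as better care, but the gap can narrow because the re-collected target fell, or because only over-qualified care declined

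*Protocol article*

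**What the plan says.** The section on the PeBeM data collection method gives the interpretation rule: "Reducing the difference between IS and OUGHT values of number, duration, and qualification can be interpreted as improving the quality of care". The Summative evaluation section and Table 2 make change in the actual-target difference, for number, duration and qualification fitting, an endpoint of its own. Table 2 also lists the shadowing indicators under quality of care.

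In the intervention group, "all elements of the data acquisition for the summative evaluation will take place as pre-post-comparison at two points in time", one year apart. Under Study design and participants, this endpoint is limited to a pre-post comparison in the intervention homes, because shadowing the control homes would have taken too many resources.

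The target has several sources. For the daily intervention plan (DIP), "Scientists from the study team (who also have an exam in nursing) and nurses from the respective nursing homes tailor an individual DIP" for each resident. The shadowers, who time the care, also judge it: "Additionally, they rate the time spent (in terms of surcharges or deductions) and the number of interventions". For qualification, Table 3 names as first source "Software derives automatically from BI", with the external assessors as determiners. Misfit has two directions, over-qualified and "underqualified (i.e., the QL is lower than required").

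The section on Algorithm 2.0 says that shadowing data, including "data on the targeted duration of specific tasks and procedures", will be used to refine the algorithm.

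**The concern.** A difference between two measured quantities can shrink because either one moves. Here both are measured again after the intervention, and the sentence credits quality of care in either case. A lower target at t1 with identical care would qualify as improvement.

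The people who set the target are not remote from the intervention. The study team develops it jointly with the homes, the homes' nurses help to write the plan behind the target number, and the shadowers are surveyed about changes they perceive as due to the intervention. Without control homes, a general shift in how targets are rated cannot be separated from a change in care.

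For qualification the difficulty is different. Fitting is the complement of two opposite misfits. Replacing over-qualified staff by fitting staff is better matching and better use of skills, but it is not by itself better care for the resident, and it can mask a rise in under-qualified care.

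At stake is what the study may say about quality of care from shadowing. Because target durations also feed Algorithm 2.0, a reader should be able to see how far they shifted between t0 and t1.

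**Working it through.** The article gives no t0 gap, misfit shares or expected change for this endpoint, so there is no planned figure to reproduce. The check sets out the sources of the target and then works through the arithmetic of the gap and of fit. All drift and share values are assumptions.

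**1. Where each target comes from (method section and Table 3)**

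- Duration: the actual value comes from time stamps and the target from the shadowers alone, as a surcharge or deduction on the time observed. On that description the duration gap is essentially the shadower's own rating.
- Number: the actual value comes from time stamps. The target comes from the DIP (determiners in Table 3: "Members of the study team qualified as a nurse") plus the shadowers' assessment.
- Qualification: the target comes first from the external assessors through software, and second from study-team determinations in the DIP where extra information was registered. Shadowers have no role.

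Rater drift is therefore a strong concern for duration, a real one for number and a weak one for qualification.

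**2. Effect of a lower target with unchanged care**

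Let A be the actual value, T the target and r = T/A at t0. The gap is T − A. If T falls by a fraction f and A stays the same, the gap falls by fT, so

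relative reduction = fT/(T − A) = r·f/(r − 1).

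The value of r is not given. I take 1.15 to 1.50, with 1.36 in between, borrowed from the 36% national staffing requirement. That figure is in full-time equivalents for a reference home; it is not the gap in these ten homes.

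| r | f = 2% | f = 5% | f = 10% |
|---|---|---|---|
| 1.15 | 15.3% | 38.3% | 76.7% |
| 1.36 | 7.6% | 18.9% | 37.8% |
| 1.50 | 6.0% | 15.0% | 30.0% |

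Worked case, r = 1.36 and f = 5%: the target goes from 1.36 to 1.36 × 0.95 = 1.292, the gap from 0.360 to 0.292, and 0.068/0.360 = 18.9%. The formula is symmetric: a target that rises by f widens the gap by the same fraction.

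**3. Effect of direction on fit**

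Fit = 1 − over-qualified share − under-qualified share. Assume 30% over and 20% under at t0:

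- t0: 1 − 0.30 − 0.20 = 50%.
- Over-qualified share halved, under-qualified unchanged: 1 − 0.15 − 0.20 = 65%.
- Over-qualified share halved, under-qualified up to 25%: 1 − 0.15 − 0.25 = 60%.

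In the last case fit rises by 10 points while under-qualified care rises by 5.

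**4. Staffing mix implied by Algorithm 1.0**

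The article gives additional requirements of 69.0% (unqualified and semi-qualified), 3.5% (qualified) and 36% overall. Solving 69.0w + 3.5(1 − w) = 36 gives a baseline lower-qualified share of w = 32.5/65.5 = 49.6%. Meeting the requirement would bring it to 0.496 × 1.69/1.36 = 61.7%. The three figures are mutually consistent. A shift of this kind makes less over-qualified care a plausible route to higher fit.

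**The case against.** The sentence is hedged and sits in a background description, and the Statistical analysis section contains no scoring rule. Table 2 lists actual and targeted number, duration and fitting as six separate indicators, and the Statistical analysis section plans to show actual and targeted aspects with their change from t0 to t1. The three fit levels are defined separately, and the shadowers record unnecessary and omitted interventions as distinct ratings. Targets are individual and needs-based, so measuring them again after a year belongs to the method, and refining the algorithm under the new work organization is a stated aim. Better matching is what the intervention is for. Much of this stands, and it rules out several stronger readings that a reader might infer:

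- That the raters are known to be unblinded. The article does not say so. It states no blinding, and the setting makes awareness likely, but that is an inference.
- That a falling target would go unseen. The separate target indicators would show it. What is missing is a rule that makes the quality claim depend on it.
- That omitted and unnecessary interventions will be offset in one net figure. No such netting is stated; it is only a reason to report them apart.
- That the move from about 50% to 62% lower-qualified staff means more under-qualified care. That mix is Algorithm 1.0's own requirement, and qualified staff also rise by 3.5%, so the inference does not follow.
- That the main analysis must be replaced by a fixed t0 standard, or that only falls in under-qualified and omitted care may count. The t0 target comes from the same kinds of raters, and needs do change.

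The objection does not remove the stated interpretation. It covers any reduction of the gap, it is attached to an endpoint without a control group, and separate tabulation does not tell the reader which kind of reduction may be called better care.

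**Conclusion.** The concern holds for the interpretation rule. As written, a lower target or less over-qualified care alone would count as better quality of care. For duration and number the mechanism is a target re-rated at t1 without a control group or a stated fixed reference. For qualification it is the merging of two opposite misfits.

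The size cannot be known from the article. If care were unchanged and targets fell by 5%, the gap would look 15% to 38% smaller for target/actual ratios of 1.50 to 1.15. This shows how sensitive the gap is; it does not predict drift, which could also go upward. A fuller protocol or analysis plan might describe blinding or the tables. That would narrow the concern but would not correct the sentence.

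**What to change.** All three changes use data already recorded and are best fixed before the t1 data are analysed.

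1. Report the t0-t1 change in the actual value, the target and the gap side by side for each component. Add a pre-specified supplementary analysis comparing t1 actual values with t0 targets by intervention type and care grade, standardised to the t1 resident mix. The analysis with re-measured targets stays.
2. Report over-qualified and under-qualified shares separately, and likewise omitted and unnecessary interventions.
3. Reword the interpretation sentence in the method section, for example: a smaller gap is read as better quality of care only when the actual value has moved toward the target and under-qualified care has not risen; a fall in over-qualified care is described as better qualification matching.

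The cost is some extra analysis and a less simple headline, with justified target revisions shown separately. The change does not alter what feeds Algorithm 2.0, but it lets readers see how far the target durations moved.
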